**CARDIOVASCULAR**				

Cardiac rhythm^2^	----	Asymptomatic, transient signs, no Rx required	Recurrent/persistent symptomatic Rx required	Unstable dysrythmia; hospitalization and Rx required
Hypertension^1^	Transient increase > 20 mmHg; no Rx	Recurrent, chronic > 20 mmHg, Rx required	Requires acute Rx; no hospitalization	Requires hospitalization
Hypotension^1^	Transient orthostatic hypotension, no Rx	Symptoms corrected with oral fluids	Requires IV fluids; no hospitalization required	Requires hospitalization

**MUSCULOSKELETAL**				

Arthralgia^2^(joint pain)	Mild pain not interfering with function	Moderate pain, analgesics and/or pain interfering with function but not with ADL	Severe pain; pain and/or analgesics interfering with ADL	Disabling pain
Myalgia^2^	Myalgia with no limitation of activity	Muscle tenderness (at other than injection ^2^site) or with moderate impairment of activity	Severe muscle tenderness with marked impairment of activity	Frank myonecrosis

**RESPIRATORY**				

Cough^3^	Mild, relieved by non-prescription medication only	Symptomatic requiring narcotic prescription medication	Symptomatic and significantly interfering with sleep or ADL	NA
Dyspnea^3^	Dyspnea on exertion, but can walk one flight of stairs without stopping	Dyspnea on exertion, but unable to walk 1 flight of stairs or 1 city block (0.1 Km) without stopping	Dyspnea interfering with ADL	Dyspnea at rest requiring oxygen therapy; intubation/ventilator indicated

^1 ^= WHO Toxicity Grading Scale; ^2 ^= DMID, NIH, Adult Toxicity Table; ^3 ^= CTCAE v3.0; *Report Grade 3 and Grade 4 adverse events to the investigators in charge.

ADL: Activities of daily living

Ref: Toxicity Grading based on CTCAE v3.0 DCTD, NCI, NIH, DHHS December 12, 2003 .

**Table 3 T3:** Toxicity grading scale for determining the severity of laboratory adverse events

**Parameter**	**Normal Range#**	**Grade for Abnormal Results (Value or Change from Reference)**			
	**(Grade 0)**	**Mild (Grade 1)**	**Moderate (Grade 2)**	**Severe (Grade 3)***	**Severe (Grade 4)***
**ALT (GPT)**	5 – 40 U/L	>ULN – 2.5 × ULN	>2.5 – 5.0 × ULN	>5.0 – 20.0 × ULN	>20.0 × ULN
**AST (GOT)**	6 – 35 U/L	>ULN – 2.5 × ULN	>2.5 – 5.0 × ULN	>5.0 – 20.0 × ULN	>20.0 × ULN
**Creatinine**	0.7 – 1.5 mg/L	>ULN – 1.5 × ULN	>1.5 – 3.0 × ULN	>3.0 – 6.0 × ULN	>6.0 × ULN
**Pancreatic Amylase**	<120 U/L	>ULN – 1.5 × ULN	>1.5 – 2.0 × ULN	>2.0 – 5.0 × ULN	>5.0 × ULN

# Normal lab ranges may vary from time to time depending on the reagent/kit used at local lab. Every time the normal ranges change, the laboratory will fax a copy of the "normal ranges" for that date to the Investigators. To respect confidentiality, the subject's name will be covered.

* Grade 3 or 4 lab value: Suspend treatment.

ULN: Upper limit of normal range

Ref: Toxicity Grading based on CTCAE v3.0 DCTD, NCI, NIH, DHHS December 12, 2003 .

1. Death

2. Life-threatening (i.e., immediate risk of death)

3. In-patient hospitalization or prolongation of existing hospitalization

4. Persistent or significant disability/incapacity

The presence of a serious adverse event that puts the patient's life at risk and/or requires immediate medical or surgical procedure will call for the discontinuation of the treatment and the initiation of the pertinent medical management of the patients. The investigator will notify the Adverse Event Committee (AEC) of the FCV of any serious adverse event within 24 hours of learning about it.

A non-serious adverse event will be classified as follows:

1. Mild: The patients are aware of their symptoms and/or signs, but those are tolerable. They do not require medical intervention or specific treatment.

2. Moderate: Patients present troubles that interfere with their daily activities. They require medical intervention or specific treatment.

3. Severe: The patients are unable to work or to attend their daily activities. They require medical intervention or specific treatment.

The possible relationship between the adverse events and the tested medication will be classified by the investigator on the basis of his/her clinical judgment and the following definitions:

1. Definitely related: Event can be fully explained by the administration of the tested medication.

2. Probably related: Event is most likely to be explained by the administration of the tested medication rather than other medications or by the patient's clinical state.

3. Possibly related: Event may be explained by the administration of the tested medication or other medications or by the patient's clinical state.

4. Not related: Event is most likely to be explained by the patient's clinical state or other medications, rather than the tested one.

All the events will be reported to the AEC that, depending on their criteria, will decide for the continuity or the withdrawal of the patient from the study and therefore the breaking of the code.

Although the project has been designed to minimize the inherent risks, any adverse event related to the study medications will be carefully evaluated by the AEC and the costs generated by the required treatment will be cover by the study.

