#### Recruitment phase

This phase will take 22 months. In the selected municipalities, the health personnel that work in hospitals and health centers will receive training regarding the disease and the study methodology. Simultaneously an epidemiological focus study will be done with the leaders of the community and the health personnel to identify the geographic and demographic conditions with the purpose of developing strategies for the recruitment of possible cases of leishmaniasis. Subsequently, the subjects that present active ulcers with more than 2 weeks of evolution, with or without parasitological confirmation of CL, will be invited by the health promoters to attend the screening visit (Table 1).

**Table 1 T1:** Schedule of activities

**PROTOCOL ACTIVITIES**	**Screening Visit**	**Initial Visit**	**Treatment visits**	**Follow-up visits**			
				**Visit 1**	**Visit 2**	**Visit 3**	**Visit 4**
**SCHEDULE OF VISITS**		0	1–20	21+3	45 ± 7	90 ± 14	180 ± 14
Clinical History	X	X		X	X	X	X
Physical Examination	X	X		X	X	X	X
Inclusion/Exclusion criteria	X						
Informed Consent	X						
Direct test	X						
Sampling of cultures		X					
Laboratory tests		X		X			
Randomization		X					
Treatment administration		X	X				
Clinical assessment of the lesion	X	X	X	X	X	X	X
Measurement of ulcers		X		X	X	X	X
Photographic registration		X		X	X	X	X
Education of patients	X	X	X	X	X	X	X
Handing over of diary		X					
Evaluation of effectiveness				X	X	X	X
Documentation of adverse events	X	X	X	X	X	X	X
Recording of concomitant medications	X	X	X	X	X	X	X

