### Initial visit

The included patients will be randomly assigned in one of two groups. A culture in Novy-Nicolle-McNeal (NNN) medium will be taken for strain identification and a blood sample withdrawn from the antecubital vein for hepatic enzymes, creatinine, and pancreatic amylase determination. During this visit, a complete medical evaluation will be performed, the ulcer will be measured and a picture will be taken. Before taking the picture, a graduated rule will be placed next to the ulcer along with a sticker marked with the identification code of the participant, and the date of the visit. The first NOP (active or placebo) will be applied covering the lesion and the first shot of meglumine antimoniate (active or placebo) administered. The patients will receive information on how not to damage the patches and how to identify and report adverse events. To help the patients to do so, they will receive a diary to register them. The two groups randomly composed will be divided as follows:

Group 1: During 20 days this group will receive simultaneously intramuscular (IM) meglumine antimoniate (Glucantime^® ^20 mg/kg/day with a maximum dose of 3 ampoules per day); and an NOP placebo.

Group 2: During 20 days this group will receive simultaneously placebo of IM meglumine antimoniate (5–15 cc/day) and an active NOP.

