### Treatment visits

The patients will visit the health center daily during 20 days to receive both the NOP (placebo or active) and meglumine antimoniate (placebo or active). Daily, the subjects and their adherence to the treatment will be assessed and the data collected. If any adverse event is detected, the patient will be referred immediately to the medical staff that will make an evaluation and report it to the adverse event committee that will take the final decision in each case.

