### Follow-up visits

This phase will last 10 months. During the follow-up, the patients will be seen by the research group in 4 opportunities. The first visit will take place the day after the end of the treatment (day 21) in which new blood samples will be taken for biochemical determinations. The second, third and fourth visits will be realized on day 45, 90 and 180 respectively. During these visits the healing process of the ulcer, the presence of recidivisms and/or reinfection and the health of the participants will be assessed. The evolution of the ulcers will be photographically registered.

The maximum and minimum diameters of the ulcer will be measured using a graduated ruler, and the induration using the ballpoint pen technique. The ulcer and induration areas will be calculated separately, and then registered in the CRF. The evaluation of the clinical response will be based on the ulcer showing the least improvement.

1. Complete clinical response: Complete reepithelization of the ulcer and disappearance of the induration.

2. Clinical Improvement: Reduction of more than 50% of the ulcer and the induration areas in relation to the last clinical evaluation.

3. Absence of clinical response: Increase or reduction of less than 50% of the ulcer and the induration areas in relation to the last clinical evaluation.

4. Therapeutic failure:

a. Increase in the size of the ulcer by more than 50% in relation to the last clinical evaluation

b. Presence of the ulcer three months after the beginning of the treatment.

c. Reactivation: Appearance of a lesion on the edge or in the center of the scar, with positive parasitological diagnosis, after a period of complete reepithelization.

d. Affection of the mucous membranes: Presence of affections of the mucous membranes during the treatment, at the end of it or in the follow-up visits.

5. Reinfection: Activation of an ulcer in an area different from the original lesion.

For subjects whose treatment will have been considered a failure the code will be broken and they will be remitted to their original health center to look for other therapeutic approach.

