### Blood samples withdrawn

Blood samples will be withdrawn from the antecubital vein to perform the following biochemical analyses:

1. Creatinine by spectrophotometry

2. Alanine transaminase (ALT) by spectrophotometry

3. Aspartate transaminase (AST) by spectrophotometry

4. Pancreatic amylase by spectrophotometry

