### Evaluation and management of adverse events

During the treatment and the follow-up visits, the patients will be asked about adverse events. Each adverse event will be classified by the physician as serious or non-serious(Table 2 and Table 3). A serious adverse event should meet one or more of the following criteria:

**Table 2 T2:** Toxicity grading scale for determining the severity of clinical adverse events

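### Baseline safety bloods are drawn at the randomisation and first-dose visit, so a patient already at Grade 3 or 4 can be randomised and dosed before the result is known

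*Protocol article*

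**What the plan says.** **The rule.** Table 3, under Evaluation and management of adverse events, grades ALT, AST, creatinine and pancreatic amylase as multiples of the upper limit of normal (ULN). Its footnote adds "Grade 3 or 4 lab value: Suspend treatment".

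**When blood is taken.** In Table 1 the row "Laboratory tests" is marked at the initial visit (day 0) and at follow-up visit 1 (day 21+3). The cells for screening and for treatment visits 1–20 are empty. The Follow-up visits section agrees: "The first visit will take place the day after the end of the treatment (day 21) in which new blood samples will be taken". The section on blood samples begins "Blood samples will be withdrawn from the antecubital vein to perform the following biochemical analyses" and lists the four assays without adding a time point.

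**What else happens on day 0.** The Initial visit section opens with "The included patients will be randomly assigned in one of two groups". It then describes the blood draw and the first patch and injection, all at that visit. It does not make the blood result a condition of randomisation or dosing.

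**Eligibility.** Table 1 and the Screening visit section place the inclusion and exclusion check at screening only. The Exclusion criteria rule out a history of hepatic, renal or cardiovascular disease but set no laboratory limit.

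**Safety surveillance during treatment.** Adverse events are elicited by questioning: "During the treatment and the follow-up visits, the patients will be asked about adverse events". At the daily visits, "If any adverse event is detected, the patient will be referred immediately to the medical staff that will make an evaluation". After that, "All the events will be reported to the AEC", the Adverse Event Committee, which may withdraw the patient.

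**The concern.** The protocol treats a Grade 3 or 4 laboratory value as reason enough to stop treatment, yet the same value at baseline does not prevent treatment from starting. The order of events is eligibility check, randomisation, blood draw and first dose, with the result seen at some unstated later time.

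This matters because the Background section lists raised hepatic aminotransferases and chemical pancreatitis among the reversible effects of antimonial treatment, and half of the patients are allocated to meglumine antimoniate. A patient with markedly abnormal liver enzymes, creatinine or amylase could receive one or more injections before anyone knew. That patient would also already be randomised, so stopping would leave a randomised patient with interrupted treatment where a simple screening exclusion was possible.

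The second aspect is what the schedule can detect later. A reader may take the footnote as laboratory protection throughout the 20 treatment days. The schedule gives no sample drawn in that period.

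**Working it through.** There is no stated figure to reproduce. The check sets the schedule beside the rule.

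**Step 1. Scheduled samples (Table 1).**

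| Visit | Day | Eligibility check | Laboratory tests | Randomisation | Treatment |
|---|---|---|---|---|---|
| Screening | none given | yes | no | no | no |
| Initial | 0 | no | yes | yes | yes |
| Treatment visits | 1–20 | no | no | no | yes |
| Follow-up 1 | 21+3 | no | yes | no | no |

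Scheduled samples per patient: 1 (day 0) + 1 (day 21+3) = 2. Scheduled samples at treatment visits 1–20: 0.

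**Step 2. Can a Grade 3 or 4 baseline value stop enrolment?** The eligibility check comes before the draw, the draw shares a visit with randomisation and the first dose, and no criterion refers to a laboratory value. As written, it cannot. It can stop treatment later, when the day-0 result is reported and the footnote applies. How many doses come first depends on the turnaround time, which is not given.

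**Step 3. Can a scheduled sample detect a rise that begins on treatment?** The window 21+3 covers days 21 to 24. Measured from treatment visit 20, that is 21 − 20 = 1 day to 24 − 20 = 4 days later. No scheduled sample can reveal such a rise while there is still treatment to suspend.

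**Step 4. Creatinine unit (minor).** Table 3 prints the normal range as 0.7–1.5 mg/L. Assumption, not from the document: the usual adult serum range has these digits in mg/dL, and 1 mg/dL = 10 mg/L. The printed ULN is 1.5, so Grade 3 starts above 3.0 × 1.5 = 4.5 and Grade 4 above 6.0 × 1.5 = 9.0, in whichever unit is meant.

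- Read as mg/dL, the limits are 4.5 and 9.0 mg/dL.
- Read as printed, they are 4.5 mg/L = 0.45 mg/dL and 9.0 mg/L = 0.90 mg/dL.
- A result of 1.0 mg/dL converted to the printed unit is 10 mg/L, and 10 / 1.5 = 6.67 × ULN, which is Grade 4.

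This misgrading arises only if a result is converted to mg/L and then set against the printed range. If result and range share a unit, or the local laboratory range is used as the Table 3 footnote on changing ranges allows, no grade changes.

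**The case against.** **The rule is not empty during treatment.** A reader might infer that the suspension rule can never act between day 1 and day 20. The document does not support that. The day-0 result may return after dosing has begun, and a Grade 3 or 4 value would then trigger suspension. An unscheduled test following an adverse-event referral could do the same. What stands is narrower: these routes act after a first dose, or after something has prompted a test, and no scheduled draw looks for a silent rise.

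**The abstract puts laboratory tests earlier.** It mentions them ahead of the criteria check and randomisation. They may be diagnostic tests. In any case Table 1 and the Initial visit section are more specific, and no criterion uses a laboratory value.

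**The article is condensed.** A procedures manual is mentioned and not shown, and it might hold dosing until results are in. That is possible. However, the point rests on a sequence the article states visit by visit, with eligibility settled before the blood is drawn.

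**Sampling frequency is a clinical choice.** There are daily visits, immediate medical referral, committee review and an exclusion for relevant medical history, and the comparator effects are described as reversible. This is a fair argument against calling the lack of a mid-treatment draw an error. It is a limitation of the schedule. The history exclusion makes a Grade 3 or 4 baseline value less likely but does not rule it out.

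**Moving the baseline draw removes the one scheduled result that could reach the rule during treatment.** True, but that result could act only on an abnormality present before treatment, and the move deals with it before any dose is given.

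**Conclusion.** The point holds as a modest patient-safety correction. Under the text as written, a patient with a Grade 3 or 4 baseline value can be randomised and dosed, and is suspended only when the result returns. All 620 planned patients follow this sequence. How many would have such a value, and how many doses they would receive first, cannot be estimated from the document.

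The lack of any scheduled sample during treatment visits 1–20 is confirmed, but as a limitation for the investigators to weigh.

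A reader might also infer that the safety comparison is biased. Nothing in the document shows this: the laboratory schedule is the same in both groups, and the point does not touch the endpoints or the sample size.

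The creatinine unit is probably a slip. That judgement rests on the assumed usual range, and the practical effect is nil where local ranges or matching units are used. It adds no weight to the main point.

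**What to change.** 1. In Table 1 and the visit text, move the existing baseline draw from the initial visit to screening, after consent and a positive parasitological result. Require the result before randomisation.
2. Add to the Exclusion criteria: Grade 3 or 4 ALT, AST, creatinine or pancreatic amylase according to Table 3.
3. Check the creatinine unit in Table 3 with the laboratory and correct it to mg/dL if confirmed.

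These are wording changes. Enrolled patients have no extra draw, since the moved sample still serves as the pre-treatment value. The cost is a delay before treatment and some patients not enrolled. Neither can be quantified, because the document gives no turnaround time, no interval between screening and the initial visit, and no frequency of Grade 3 or 4 values. Those excluded leave before randomisation, so nobody is randomised and then left untreated for this reason.

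This change does not detect a rise that begins on treatment. That would need a draw during days 1–20, one added procedure per patient, and the decision is a clinical one for the investigators.

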### Data analysis phase

This phase will last 6 months. After completing all the data entry to the CFR, the results will be audited and the detected errors evaluated and corrected by the person in charge. The information will be entered in two different databases by two different people and the records will be compared to detect any discrepancy. The original CFR will be used to correct any mistake in the database.

For the statistical analysis, Stata 8.0 will be used. The descriptive analysis will be composed of medians and proportions according to the nature of the variables, with its respective 95% confidence intervals. As a dispersion measurement the standard deviation will be calculated. The distribution of the variables will be studied using the Shapiro-Wilk test. To detect any difference between the groups, a T-test or a Wilcoxon test will be performed according to its distribution. The categorical variables will be compared using the Chi2 test or the exact Fisher's test. If required, a model of multiple logistic regressions or a covariance analysis will be done.

Two interim analyses will be performed when 35% and 70% of the calculated sample is collected, with the objective of determining the differences in effectiveness and safety between the treatments.

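### A normality pre-test picks the test for continuous variables and baseline adjustment is optional, although day-0 laboratory values and ulcer size are collected

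*Protocol article*

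**What the plan says.** The rule stands in the protocol article under 'Data analysis phase'. It has two steps. First, "The distribution of the variables will be studied using the Shapiro-Wilk test". Then, "To detect any difference between the groups, a T-test or a Wilcoxon test will be performed according to its distribution". No cut-off for the pre-test is given, and the variables are not named. Categorical outcomes have their own sentence: "The categorical variables will be compared using the Chi2 test or the exact Fisher's test". Adjustment is conditional: "If required, a model of multiple logistic regressions or a covariance analysis will be done".

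Elsewhere the article collects what an adjusted analysis needs:

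- **Laboratory values.** 'Initial visit' provides for "a blood sample withdrawn from the antecubital vein for hepatic enzymes, creatinine, and pancreatic amylase determination". 'Follow-up visits' adds a day-21 visit "in which new blood samples will be taken for biochemical determinations". Table 1 shows these two laboratory time points and no others.
- **Ulcer size.** At the initial visit "the ulcer will be measured and a picture will be taken". For follow-up, "The ulcer and induration areas will be calculated separately, and then registered in the CRF". Table 1 lists ulcer measurement at day 0 and at all four follow-up visits.

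**The concern.** A t-test compares means and a Wilcoxon test compares ranks. If the observed distribution decides between them, the plan does not fix what is being compared, and the Wilcoxon p-value carries no between-group effect in the variable's own units. Shapiro-Wilk is also sensitive at this sample size: it rejects for skewness too mild to trouble a t-test.

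Second, the default comparison is unadjusted. Enzyme levels and ulcer areas usually depend on where the patient started, so a model with the day-0 value gives a narrower interval from the same patients. Comparing adverse events with antimony is the second specific objective, and the Background section names raised aminotransferases and chemical pancreatitis among the harms of antimony. Precision on ALT, AST, creatinine and amylase therefore matters for the safety claim.

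**Working it through.** The article gives no SD, effect size, power or baseline correlation for any continuous variable, so there is no figure of its own to reproduce here. Its 558 (620 after losses) belongs to the binary success endpoint and does not enter this check.

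**Inputs.** From 'Sample size': 558/2 = 279 per arm before losses, and 310 × 0.95 = 294.5 after the stated 5% loss. I use 279 or 290 per arm. From 'Data analysis phase': looks at 35% and 70%, taken as 0.35 × 558 ≈ 195 and 0.70 × 558 ≈ 391 patients. Assumed: Shapiro-Wilk cut-off 0.05, two-sided 5% tests, a shift of 0.2 SD on the log scale, and a correlation ρ between day-0 and later value of 0.3, 0.5 or 0.7.

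**1. Which test the rule selects.** Share of simulated data sets in which Shapiro-Wilk rejects, both arms pooled:

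| Distribution | 98 per arm | 279 per arm |
|---|---|---|
| Normal | 5% | 5% |
| Gamma, shape 20 (mild skew) | 60% | 98% |
| Lognormal, log SD 0.5 or 1 | 100% | 100% |
| 80% zeros, rest lognormal | 100% | 100% |

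In single samples of 300 from a lognormal distribution, rejection was about 78% to 81% at a coefficient of variation of 15%, 96% to 97% at 20%, and 100% at 31%. Skewed variables therefore go to Wilcoxon almost without exception.

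For mildly skewed variables the choice can change as data accrue. With coefficients of variation of 8% to 15%, the selected test was not the same at 195, 391 and 558 patients in 38% to 51% of simulations.

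**2. Type I error.** Across six distributions at 98 and 279 per arm (4,000 replicates each), the two-stage procedure rejected a true null in 0.043 to 0.056 of trials. The Monte Carlo standard error is √(0.05 × 0.95/4000) = 0.0034, so this is compatible with 5%.

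**3. Precision from baseline.** With ANCOVA the variance of the treatment contrast is multiplied by 1 − ρ². A test on change from day 0 has factor 2(1 − ρ).

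| ρ | Later value only | Change from day 0 | ANCOVA |
|---|---|---|---|
| 0.3 | 1.00 | 1.40 | 0.91 |
| 0.5 | 1.00 | 1.00 | 0.75 |
| 0.7 | 1.00 | 0.60 | 0.51 |

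The reduction against the later value alone is 9%, 25% and 49%. The difference detectable with 80% power at 279 per arm is (1.960 + 0.842) × √(2/279) = 0.237 SD unadjusted. Multiplied by √(1 − ρ²), it becomes 0.226, 0.205 and 0.169 SD.

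**4. Power for a 0.2 SD shift, 290 per arm.** The standardised effect is 0.2 × √(290/2) = 2.408.

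- Wilcoxon on the later value (efficiency 3/π = 0.955): Φ(2.408 × √0.955 − 1.96) = 65%.
- t-test on the log of the later value: Φ(2.408 − 1.96) = 67%.
- ANCOVA, ρ = 0.3: Φ(2.408/√0.91 − 1.96) = 71%.
- ANCOVA, ρ = 0.5: Φ(2.408/√0.75 − 1.96) = 79%.
- ANCOVA, ρ = 0.7: Φ(2.408/√0.51 − 1.96) = 92%.

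Simulation agrees: about 65% for Wilcoxon, and 70% to 71%, 78% to 79% and 92% for ANCOVA. Of the gain, about 2 points come from leaving ranks for the log scale, which holds when the log values are near normal. The rest comes from baseline.

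**5. Ulcer area late in follow-up.** The assumed success rates are 85% and 75%, and success requires complete re-epithelialisation at three months. About (85 + 75)/2 = 80% of day-90 areas would then be zero. An ANCOVA of log(area + 1) on such data depends on the unit of area and does not yield a true ratio of geometric means.

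**The case against.** The strongest reply is that the article does not do what a quick reading suggests.

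- **Baseline is not ruled out.** One might infer that day-0 values are ignored and only the later value is tested. The text says neither. It allows a covariance analysis, and it leaves open whether the two-sample test is applied to later values or to changes. This stands, so the point is limited to adjustment being optional and undefined. A change score would not close the gap: in the table above ANCOVA has the smaller variance at each correlation.
- **Covariate lists belong in an analysis plan that is not shown.** Fair, and a missing list alone would be no finding. But the pre-test and the condition on adjustment are choices that the article states.
- **The variables are inferred.** This stands. The sentence does not name ulcer area or laboratory values; the link comes from the schedule. Laboratory toxicity is also graded (Table 3) and ulcer response is put into categories, and those comparisons go to chi-square or Fisher.
- **Wilcoxon is a valid test for skewed data.** True. If the rule nearly always picks it, the practical discretion is small for strongly skewed variables. The article's medians with confidence intervals are in original units, though they describe each group and are not a contrast.
- **Data-driven choice of test suggests excess false positives.** A reader might infer this, but the simulations show none.
- **Different tests at different visits.** This cannot happen for laboratory values, which have one post-treatment measurement. It could happen between the interim looks and the final analysis, and only for mildly skewed variables.

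**Conclusion.** The concern holds as a minor point on continuous safety and secondary comparisons. The article fixes a data-dependent test where a named method would serve better, and it leaves baseline adjustment to an undefined condition although the baseline is already collected.

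The size depends on a correlation that the documents do not give. At 0.3 the gain is modest, from about 65% to about 71% power for a 0.2 SD shift. At 0.7 it is large, about 92%. The shift and the lognormal shape are also assumptions, and the article sets no power target for these variables, so no design promise is broken.

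Nothing here touches the binary success endpoint, its chi-square or Fisher comparison, or the sample size.

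**What to change.** In 'Data analysis phase', drop the Shapiro-Wilk rule and the if-required condition for these variables, and name one method for each:

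- **Day-21 ALT, AST, creatinine and amylase:** ANCOVA on the log scale with the log day-0 value as covariate, reported as ratios of geometric means with 95% confidence intervals. Wilcoxon serves as a sensitivity check. The comparison of graded toxicity stays as it is.
- **Ulcer area at early visits, where few ulcers have healed:** ANCOVA adjusted for day-0 area. List these visits in advance, since choosing them from the observed healing would bring back a data-dependent rule. The article gives no expected healing rate before three months.
- **Ulcer area at day 90 and later:** a prespecified rank-based comparison, or the binary healing outcome alone.

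Use the same method at both interim looks and at the final analysis. The cost is wording only, with no new visits, samples or patients. The one small burden is a stated, simple handling of patients without a day-0 value.
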